### Qualitative approach

At the pre-surgery assessment (T1) a sub-cohort of the study’s participants will take part in a semi-structured interview to feedback on how the PRE-HIIT study has impacted on their preparation for surgery. Interviews will be held with approximately 20 participants or until data saturation is reached.

### Adherence

Adherence to the exercise component of PRE-HIIT will be measured with traditional adherence variables i.e. attendance at supervised sessions and completion of home-based sessions and monitoring of compliance to the prescribed exercise protocol. Compliance to the aerobic component will be documented by the achieved heart rates on the Polar Heart Rate Monitors, and the duration of aerobic exercise, and for resistance training, the weight, number of sets, and repetitions will be recorded. During the supervised sessions compliance will be monitored by the supervising physiotherapist, whilst during homebased sessions participants will record their compliance in a home exercise diary. PRE-HIIT will implement a series of drug trial adapted adherence outcomes as described by Nilsen et al. [30]. These additional exercise adherence variables will include; permanent treatment discontinuation, treatment interruption, dose modification, early session termination, and pre-treatment intensity modification. Adherence variables are described fully in Table 1.

### Hospital resources

The costing of hospital stays, and interventions will be carried out based on activity data from hospital records, with unit costs taken from the standard estimated costs from the Healthcare Pricing Office. Programme implementation costs will be analysed in consideration of clinician salaries, overheads and equipment costs. Formal care costs will be extracted from medical charts and from the institutional database in consideration of preoperative characteristics, surgery type and postoperative recovery including complications. Since the participants in the study are randomised to each arm, the comparison of costs of hospital stays will be reported as differences and the normal tests of significance. It is also important to assess if the intervention has longer term effects beyond hospital discharge. The destination at discharge, use of community health services from the time of discharge to the follow up outpatient appointment and EQ5D5L scores at the time of the follow up appointment will be collected for each participant. This will allow the measurement of any effects of the intervention on the feasibility of the patient going home directly from hospital, and any difference in the need for community health services. The EQ5D5L scores at outpatient follow up will allow an assessment if any short-term difference persists and will assist in modelling the likely medium-term effect of the intervention on costs and QOL.

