**Methods:**

The PRE-HIIT Randomised Controlled Trial (RCT) will compare a 2-week high intensity interval training (HIIT) programme to standard preoperative care in a cohort of thoracic and oesophageal patients who are > 2-weeks pre-surgery. A total of 78 participants will be recruited (39 per study arm). The primary outcome is cardiorespiratory fitness. Secondary outcomes include, measures of pulmonary and physical and quality of life. Outcomes will be measured at baseline (T0), and post-intervention (T1). Post-operative morbidity will also be captured. The impact of PRE-HIIT on well-being will be examined qualitatively with focus groups/interviews post-intervention (T1). Participant’s experience of preparation for surgery on the PRE-HIIT trial will also be explored. The healthcare costs associated with the PRE-HITT programme, in particular acute hospital costs, will also be examined.

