Cardiopulmonary fitness is an established indicator of postoperative outcome and surgical candidacy. In intra-abdominal surgery, low cardiopulmonary fitness, characterised by an anaerobic threshold (AT) < 11 ml/kg/min provides the most accurate indicator of postoperative morbidity and hospital LOS [8]. Comparably, peak oxygen consumption (VO2peak) < 10 ml/min/kg is predictive of mortality and serious morbidity following major thoracic operations [9]. While a relatively weak association is reported between cardiopulmonary fitness and oesophagectomy outcome specifically [1, 8], it follows from the robust thoracic and intra-abdominal literature that preoperative fitness is an important determinant of oesophagectomy outcome. Furthermore, as oesophageal cancer management moves towards multimodality [3], the attrition impact of preoperative chemo(radio)therapy leads to considerable physical deconditioning and loss of preoperative fitness thus compromising post-operative outcome [10]. In a multivariate analysis, a 1.0 ml/kg/min increase in fitness reduced the odds of complications following colorectal resection by over 20% (OR 0.77 (95% confidence interval (CI) 0.66–0.89) while an increase of 2.0 ml/kg/min was associated with a 40% reduction (OR 0.6 (95%CI 0.45–0.80) [11]. In intra-abdominal surgery, prehabilitation involving inspiratory muscle training (IMT), aerobic exercise and resistance training reduces the incidence of postoperative complications by 41% (OR 0.59 (95%CI 0.38–0.91), with the strongest impact observed in relation to PPCs specifically [12].

While the evidence in intra-abdominal surgery is encouraging, little is known about exercise prehabilitation for major thoracic operations on the lung or oesophagus. Preliminary results from moderate-to-vigorous intensity aerobic exercise programmes prior to thoracotomy for lung cancer have reported improvements in pre-operative cardiopulmonary fitness, and QOL, however trials are limited by single-armed designs and low participant numbers [13]. Exercise prehabilitation for oesophagectomy has typically prescribed IMT, a form of exercise training which strengthens the inspiratory muscles. While initial results from IMT trials were encouraging, a randomised trial of 246 patients, reported no reduction in pneumonia rates or PPCs following oesophagectomy with IMT [14], highlighting the need to prescribe more intensive exercise training to achieve a higher training stimulus for clinical impact.

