### Sample size calculation

The primary response is the change in VO_2_peak from baseline (T0) to post-intervention (T1). On the basis of estimates calculated from our pilot study, a sample of size 64 (32 in each arm) is needed in order to detect a mean difference in VO_2_peak of 1 ml/kg/min between the control and intervention groups (assuming a standard deviation of change in VO_2_peak of 1.4 ml/kg/min for each arm) with 80% power at the 5% significance level based on a two-sample t-test. Based on the results from the PHIIT trial and others [16, 17], an improvement of 1 ml/kg/min in VO_2_peak is feasible with the exercise intervention prescribed. It is anticipated that the active control group will not experience a change in fitness during this 2 week time period [16]. Moderate intensity exercise interventions have not been shown to significantly change preoperative aerobic capacity and functional capacity of patients due to undergo elective surgery [31].

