### Statistical analysis

Quantitative data analysis will be performed using R IBM SPSS software, employing statistical best practice. A comparison of patient characteristics at baseline will be carried out for each arm. Summary statistics for continuous variables (means and standard deviations or median and ranges as appropriate) and categorical variables (counts and proportions) will be presented. Graphical summaries (boxplots, case profile plots, labelled scattered plots) will be used to compare the distribution s of each response variable and for patient characteristics between the arms. A linear mixed model will be used to model the longitudinal change in the primary response between the groups, allowing for missing data (under the assumption that data are missing at random) and allowing for within subject correlations in the repeated measures across time. The model will adjust for the baseline response variable and other covariates as necessary.

A qualitative approach will be taken to gather participants’ feedback on how the PRE-HIIT study has impacted on their preparation for surgery. Data collection will take a semi-structured approach individual interviews following the intervention. The discussion guide for the interviews will explore topics such as: the impact of the intervention on health, well-being, and activities of daily living, facilitators and barriers to preoperative exercise, and recommendations for future implementation of the programme. Interviews will be digitally audio-recorded and transcribed verbatim for data analysis. A qualitative descriptive approach [32] will be taken to the analysis, with the aim of providing a substantial description of what the participants said, without drawing deep implications from the data. Braun and Clarke’s 6 stage approach to thematic analysis will be used to analyse all data collected [33]. A team of researchers will analyse all transcripts following an agreed process using nVivo 12 (QSR International, Australia).

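### Hospital cost is compared as a simple arm difference when a pre-specified T0 VO2peak covariate, already collected in everyone, could add modest precision at no data cost

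*Protocol article*

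**What the plan says.** The Hospital resources section gives randomisation as its reason and then states that "the comparison of costs of hospital stays will be reported as differences and the normal tests of significance". Preoperative characteristics and surgery type appear in the same section, but as items considered when formal care costs are extracted, not as terms in a model.

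The Background holds that "Cardiopulmonary fitness is an established indicator of postoperative outcome and surgical candidacy", and the Abstract also calls pre-operative fitness an established predictor. The Background adds a caveat: for oesophagectomy specifically, the reported association is relatively weak.

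Baseline adjustment is described only in the Statistical analysis section, for the linear mixed model of the primary response: "The model will adjust for the baseline response variable and other covariates as necessary".

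The randomisation section places the T0 assessment before allocation and names no stratification factor. Completing a cardiopulmonary exercise test is an inclusion criterion, and the Safety section makes formal enrolment conditional on it.

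**The concern.** The cost method is stated together with its reason, so this is not silence left to an analysis plan. The reason is incomplete. Randomisation makes the simple difference unbiased over repeated trials. It does not make a prognostic baseline measurement useless, and it does not prevent chance imbalance in one trial with 39 per arm.

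The protocol's own argument links fitness to complications and length of stay, and those to cost. If that holds in this population, T0 VO2peak explains part of the variation in cost, and a comparison that ignores it has a wider confidence interval than necessary. If the arms happen to differ in T0 fitness, part of the observed cost difference will reflect that. Without a rule fixed beforehand, a visible imbalance in the baseline table would also invite a choice between raw and adjusted results after the data are seen.

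**Working it through.** **1. The plan's own figure.** The only stated sample size is for VO2peak: "a sample of size 64 (32 in each arm) is needed". Its inputs, all from the Sample size calculation section, are a target difference of 1 ml/kg/min, an SD of change of 1.4 ml/kg/min per arm, power of 80%, a 5% level and a t-test. Taking the test as two-sided (not stated), the normal approximation is 2 × (1.960 + 0.842)² × 1.4² / 1² = 30.8, so 31 per arm. The exact t-test needs 31.76, so 32 per arm, with power 80.3%. The figure of 64 is reproduced. No size or power is stated for cost. Recruitment is 39 per arm ("A total of 78 participants will be recruited (39 per study arm").

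**2. Chance imbalance in T0 VO2peak.** The SD is assumed, because the article gives none. SE = SD × √(2/n); P(|imbalance| ≥ 1) = 2 × [1 − Φ(1/SE)].

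| Assumed T0 SD (ml/kg/min) | SE, 39 per arm | P(≥ 1), 39 per arm | P(≥ 1), 32 per arm |
|---|---|---|---|
| 2 | 0.45 | 2.7% | 4.6% |
| 3 | 0.68 | 14.1% | 18.2% |
| 4 | 0.91 | 27.0% | 31.7% |
| 5 | 1.13 | 37.7% | 42.4% |
| 6 | 1.36 | 46.2% | 50.5% |

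A partial cross-check is possible. If the SD is the same at T0 and T1, the SD of change of 1.4 implies a T0 SD of 1.4/√(2(1 − ρ)), where ρ is the T0–T1 correlation. That is 2.2, 3.1 and 4.4 for ρ = 0.80, 0.90 and 0.95. With 39 per arm, the first and last give SEs of 0.50 and 1.00, and probabilities of about 5% and 32%.

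**3. Precision gained by adjustment.** With r the correlation of T0 VO2peak with cost (assumed), the variance of the arm difference is multiplied by 1 − r².

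| r | Variance cut | Relative CI width, √(1 − r²) | 78 patients act like, 78/(1 − r²) | Power, if 80% unadjusted |
|---|---|---|---|---|
| 0.1 | 1% | 0.995 | 78.8 | 80.4% |
| 0.2 | 4% | 0.980 | 81.2 | 81.6% |
| 0.3 | 9% | 0.954 | 85.7 | 83.6% |
| 0.4 | 16% | 0.917 | 92.9 | 86.4% |
| 0.5 | 25% | 0.866 | 104.0 | 89.9% |

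Estimating the slope costs a little. For a normally distributed covariate the variance rises on average by (78 − 3)/(78 − 4) = 75/74, about 1.4%. At r = 0.1 the net factor is 0.99 × 75/74 = 1.003, which is no gain at all.

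**4. Effect of an imbalance of exactly 1 ml/kg/min.** The simple cost difference moves by (r/SD)/√(2/39) of its own standard error. This runs from 0.15 (SD 6, r 0.2) to 0.74 (SD 3, r 0.5). Type I error given that imbalance is about 4% to 8%; averaged over randomisations it stays at 5%.

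**5. Order of magnitude in money.** This is illustrative only, since the inputs come from different populations. The Background's odds ratio of 0.77 per ml/kg/min (colorectal resection), applied to a 25% complication rate (pulmonary complications after thoracic surgery), gives odds of 0.333 × 0.77 = 0.257, a rate of 20.4% and a drop of 4.6 points. At the $20,777 increment (serious complications after oesophagectomy) that is about $951 per patient. Assume base cost is lognormal with median $31,375 and log-SD 0.35, with the increment added in 25% of patients. The cost SD is then √(12,042² + 8,997²), about $15,000, and the SE of the arm difference is 15,000 × √(2/39), about $3,400. The shift is 951/3,400 = 0.28 SE.

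**The case against.** The strongest reply is that nothing here is an error. A difference between randomised arms is unbiased, and its standard error already allows for chance imbalance in every prognostic factor. A reader might infer from the imbalance probabilities that the cost comparison is biased, or that an imbalance as large as the treatment effect is to be expected. The article supports neither: unconditional type I error is 5%, and the probability depends on an SD that it does not give. This part of the reply stands in full.

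Second, the gain is small. The illustrative $951 is about a quarter of a standard error, and at r = 0.2 to 0.3 the confidence interval narrows by only 2% to 5%. The article itself reports a weak link for oesophagectomy, and no correlation with cost is given for either type of surgery. This also stands, and it sets the severity.

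Third, a reader might extend the point to complications and length of stay. The outcome sections state no analysis for these, so there is nothing to correct.

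Fourth, the wording does not literally say unadjusted, and covariates are often left to an analysis plan. This carries less weight. The sentence fixes a difference with ordinary significance tests and rests it on randomisation, which is a stated choice rather than an omission.

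**Conclusion.** The point holds as a modest, optional gain in precision for the hospital-cost comparison. The stated method is valid, but it leaves unused a baseline measurement that is already collected in everyone and that the protocol itself regards as prognostic.

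The benefit rests on two unknowns, the T0 SD and its correlation with cost. It ranges from nothing at r = 0.1 to a variance cut of about one quarter at r = 0.5. The lower end is more plausible for oesophagectomy, given the article's own caveat. Severity is low: no conclusion about cost is shown to be at risk, and the case for the change is that it is nearly free.

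**What to change.** In Hospital resources, replace the simple comparison with a pre-specified linear regression of hospital cost on arm, with T0 VO2peak as a fixed covariate. For oesophageal patients who are also tested at diagnosis, specify the T0 value. Surgery type (oesophagectomy or lung resection) is also known at baseline and can be added. Report the adjusted mean cost difference with a 95% CI, and keep the unadjusted difference as supportive. Fixing this before the data are seen also removes any later choice between the two.

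The cost is a sentence or two of analysis wording and one degree of freedom (a second if surgery type is added), with no new data.

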### Safety

Prior to baseline testing, all participants will require written medical approval confirming their suitability for participation. Patients will only be formally enrolled on the study after successfully completing a CPET with ECG monitoring. All CPET will be medically supervised and will take place in the CRF which is located within SJH and is covered by the hospital’s emergency response team. All adverse events will be recorded, and serious adverse events will be reported to the research ethics committees.

### Sample size calculation

The primary response is the change in VO_2_peak from baseline (T0) to post-intervention (T1). On the basis of estimates calculated from our pilot study, a sample of size 64 (32 in each arm) is needed in order to detect a mean difference in VO_2_peak of 1 ml/kg/min between the control and intervention groups (assuming a standard deviation of change in VO_2_peak of 1.4 ml/kg/min for each arm) with 80% power at the 5% significance level based on a two-sample t-test. Based on the results from the PHIIT trial and others [16, 17], an improvement of 1 ml/kg/min in VO_2_peak is feasible with the exercise intervention prescribed. It is anticipated that the active control group will not experience a change in fitness during this 2 week time period [16]. Moderate intensity exercise interventions have not been shown to significantly change preoperative aerobic capacity and functional capacity of patients due to undergo elective surgery [31].

### Statistical analysis

Quantitative data analysis will be performed using R IBM SPSS software, employing statistical best practice. A comparison of patient characteristics at baseline will be carried out for each arm. Summary statistics for continuous variables (means and standard deviations or median and ranges as appropriate) and categorical variables (counts and proportions) will be presented. Graphical summaries (boxplots, case profile plots, labelled scattered plots) will be used to compare the distribution s of each response variable and for patient characteristics between the arms. A linear mixed model will be used to model the longitudinal change in the primary response between the groups, allowing for missing data (under the assumption that data are missing at random) and allowing for within subject correlations in the repeated measures across time. The model will adjust for the baseline response variable and other covariates as necessary.

A qualitative approach will be taken to gather participants’ feedback on how the PRE-HIIT study has impacted on their preparation for surgery. Data collection will take a semi-structured approach individual interviews following the intervention. The discussion guide for the interviews will explore topics such as: the impact of the intervention on health, well-being, and activities of daily living, facilitators and barriers to preoperative exercise, and recommendations for future implementation of the programme. Interviews will be digitally audio-recorded and transcribed verbatim for data analysis. A qualitative descriptive approach [32] will be taken to the analysis, with the aim of providing a substantial description of what the participants said, without drawing deep implications from the data. Braun and Clarke’s 6 stage approach to thematic analysis will be used to analyse all data collected [33]. A team of researchers will analyse all transcripts following an agreed process using nVivo 12 (QSR International, Australia).

### Data monitoring

Data monitoring will be provided by the trial steering committee, including overall project supervision, progress monitoring, advice on scientific credibility and ensuring the integrity and appropriate running of the project. The research team will make quarterly reports to the trial steering committee.

### Dissemination

Findings of PRE-HIIT will be disseminated via peer-reviewed publications and conference presentations. Aggregate study results will be presented to participants and their families at an education symposium upon study completion. Anonymised data will be made available on an open access repository.

### Public and patient involvement (PPI)

PRE-HIIT will involve a number of PPI initiatives. We will seek feedback on participant documentation, particularly the participant information leaflet and consent form, to ensure readability and clarity. In addition, a patient representative will be invited to speak at the education symposium in the final year of the project.

### Study status

PRE-HIIT will begin in recruitment in 2020.

## Discussion

The PRE-HIIT RCT will examine the influence of pre-operative high intensity interval training programme on physiological outcomes and postoperative recovery and, through evaluation of health economics, the impact of the programme on hospital costs**.**

There is a need for clinically feasible interventions that attenuate the impact of multiple therapeutic interventions, most particularly major oncological operations, and accelerate patient recovery. Prehabilitation is likely to have its greatest impact in cancer populations who experience the greatest treatment morbidity, such as oesophageal and lung cancer. There is growing interest in the value of exercise prehabilitation to increase preoperative fitness above critical values in oncologic resections [15]. HIIT exercise training stimulates great improvements in cardiopulmonary fitness over short periods compared to continuous aerobic training and therefore may be ideally suited to exercise prehabilitation. This mode of exercise prehabilitation may attenuate postoperative risk and improve postoperative recovery, thus improving patient quality of life and having considerable economic benefits for the healthcare system. Given the high unit cost of hospital days and procedures, the direct effects of the intervention on hospital costs and any evidence of differences in QOL which will be explored by the PRE-HIIT trial are of considerable interest. The results of this study will inform current perioperative practice and will provide direction for future research.

## Data Availability

Not applicable.

## Abbreviations

CPET: Cardiopulmonary exercise test
CRF: Clinical research facility
ERAS: Enhanced recovery after surgery
HIIT: High intensity interval training
LOS: Length of stay
LT: Lactate threshold
POD30: Post-operative day 30
PPI: Public and patient involvement
QOL: Quality of life
RCT: Randomised controlled trial
VATS: Video assisted lobectomy
VT: Ventilatory threshold
